## Abstract

Neurogenic cervical spondylosis is the most common type of cervical spondylosis, accounting for approximately 60% percent of the incidence of cervical spondylosis. Cervical spine Long manipulation and sling exercise training (SET) have obtained good therapeutic results in clinical rehabilitation. The aim of this study was to evaluate the effect of Long manipulation combined with SET on neurogenic cervical spondylosis. In this assessor-blind, randomized controlled trial, 90 eligible patients will be randomized into a combination treatment group (Long manipulation combined with SET), a Long manipulation group and a conventional massage group. The visual analogue score, the Neck Disability Index score, and muscle fatigue in the bilateral upper oblique and Musculus sternocleidomastoideus, using mean power frequency and median frequency from the surface electromyography frequency domain index, will be assessed before and after the intervention at 0 and 4 weeks, respectively.

**Trial registration:** Registered in the Chinese Clinical Trial Registration Center with the number ChiCTR2100054978. Registered December 30, 2021.

## Introduction

1

Research has confirmed that the degree of muscle fatigue is also associated to its stiffness, which is a manifestation of muscle tension and increases as muscle fatigue increases. The onset of cervical spondylosis is the result of a series of symptoms and signs caused by an imbalance between the cervical vertebrae and the adjacent soft tissues, and is the result of muscle fatigue caused by long-term tension in the neck and shoulder muscles.^[1]^ Due to degenerative changes in the cervical intervertebral discs, growth of the hook or synovial joints, and hypertrophic bone spurs protruding laterally, the nerve roots at the corresponding level are stimulated or compressed, and a series of diagnostic manifestations of nerve root irritation or dysfunction of the corresponding segment occur, characterized by pain in the back of the shoulder, radiating pain in the upper limbs and fingers, numbness and weakness, etc, which are more common unilaterally, and the prognosis is mostly good, but these clinical symptoms seriously affect people's quality of life.^[2]^

At present, there are many nondrug conservative treatment methods, such as acupuncture, massage, herbal compresses, low frequency therapy, and microwaves, all of which are effective. Numerous studies have shown that the clinical efficacy of conservative treatment and surgical treatment is the identical.^[3]^ Therefore, it is important to investigate how best combined conservative treatment can be used to improve neck pain and nerve root symptoms in patients with radiculopathy and to alleviate the progression of cervical spondylosis.

Sling exercise training (SET) stresses the use of the patient's own gravity to adjust the overall biomechanics.^[1]^ It is a closed chain exercise, based on neuromuscular stimulation, to adjust the central nervous system's control of the muscles and regain function to the inactivated local stabilizing muscles. It is also a painless form of closed chain training in both “hold” and “repetition” to stimulate the deeper stabilizing muscles of the cervical spine, ultimately re-establishing the appropriate muscle control pattern to enhance the stability of the cervical spine, so that the weak chains of the muscles that make up the “upper cross” are strengthened and their compensation is relieved. The treatment therefore trains the weak chain of muscles, while improving local pain and stiffness, and thus relieving fatigue.^[1]^ There are some studies have shown that osteopathic manipulation can adjust the static balance of spinal, while tendon manipulation can adjust the dynamic balance of the neck.^[4]^ Long manipulation combines osteopathic manipulation and tendon manipulation to bring the local imbalanced bio-mechanical equilibrium into balance, release the nerve roots and their surrounding soft tissue adhesion, change the area of the intervertebral space, adjust the relationship between the hook vertebral joints, link muscle spasm, release synovial inclusions, adjust the pressure distribution of the cervical spine tissues, enhance the stability of the cervical spine, and restore the normal physiological curvature of the cervical spine.^[5]^ Therefore, this study will use SET combined with Long manipulation to observe its effect on improving pain, cervical spine function, and muscle fatigue in patients with neurogenic cervical spondylosis (NCS).

## Method/design

2

The study was an assessor-blind, single-center randomized controlled trial. The aim of this study is to investigate the effect of SET combined with Long manipulation on pain, cervical function and muscle fatigue in patients with CRS. The project leader will be responsible for the overall project and will initiate the establishment of the subject project team. The subject project team will be responsible for subject security, recruitment and treatment and assessment, and quality control. The coordinating center staff will be responsible for communication of protocol changes and provision of information. The trial will have a 4-week period. After randomization, subjects will conduct assessments of primary and secondary indicators in 2 phases at 0 and 4 weeks (Fig. 1; Additional File 1).

**Figure 1 F1:**
[figure not shown]
Consort diagram flowchart. MF = median frequency, MPF = mean power frequency, NDI = Neck Disability Index, SMEG = surface electromyography, VAS = visual analogue score.

### Eligibility criteria

2.1

#### Inclusion criteria

2.1.1

1.The selected patients must meet the diagnostic criteria for NCS as revised in the Second National Symposium on Cervical Spondylosis in 1993 and the modified criteria in the minutes of the Third National Symposium on Cervical Spondylosis in 2008^[6]^;2.Having more typical ridiculous symptoms such as pain and numbness in the arm, the extent of which corresponds to the area innervated by the cervical spinal nerve;3.The patient has functional limitation of neck movement and pressure pain in the spine process of the dysfunction vertebrae, para-vertebral area, and the internal superior scapular angle of the affected side;4.A positive cervical compression test and/or brachial plexus nerve pull test;5.The imaging findings are consistent with diagnosis presentations.

#### Exclusion criteria

2.1.2

1.Patients with serious chemical diseases.2.Patients with severe osteoporosis, anthropolising spondylitis, neoplasms, fractures and other pathologies.3.Those who do not collaborate with study.

Any potential subjects who meet the inclusion and exclusion criteria will be recruited from the outpatient and inpatient departments of the Department of Rehabilitation Medicine at Ningbo Haishu Rehabilitation Hospital. Potential subjects who meet the requirements will be interviewed by the research staff and informed of the inclusion criteria and procedures. Eligible subjects will first be analyzed through a baseline assessment and then diagnosed based on clinical presentation and physical examination, combined with imaging studies. Subjects will be informed that participation in the trial is strictly voluntary and that they can quit from the trial at any time. If you withdraw, the data collected will not be removed and will be used for the final statistical analysis. A summary table of data containing all variables and potential risks will be created by the research center. The raw information obtained will be stored in an electronic database for subsequent statistical analysis. Subject recruitment for the study will begin on December 31, 2021. A flow chart of the trial for subjects is shown in Figure 1.

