#### Randomization, allocation, and blinding

2.1.5

In this study, randomization was carried out using a table of random values compiled by SPSS 23.0 software, and the patients were randomly divided into 3 groups with a 1:1:1 allocation ratio: the combined treatment group (30 cases), the Long manipulation group (30 cases) and the control group (30 cases). Only the principal investigator in this study will be aware of the order of random assignment. The assessor will be a trained external rehabilitation therapist. The assessor and the patient will not be able to communicate about the intervention during the assessment. In this study, only the assessors were blinded and therefore the study did not involve the process of unblinding.

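### Other neck treatment, which the protocol itself calls effective, is neither held constant nor recorded in an inpatient and outpatient sample, so use that differs by arm after randomisation could bias the 4-week contrasts undetected

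*Protocol article*

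**What the plan says.** All of this is in the protocol article.

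- **Recruitment (2.1.2).** Patients who meet the criteria "will be recruited from the outpatient and inpatient departments of the Department of Rehabilitation Medicine" of one hospital.
- **Eligibility (2.1.1 and 2.1.2).** The five inclusion criteria concern diagnosis, symptoms, signs, provocation tests and imaging. The three exclusions are serious disease, "Patients with severe osteoporosis, anthropolising spondylitis, neoplasms, fractures and other pathologies", and "Those who do not collaborate with study". None concerns treatment that the patient is receiving or has recently received.
- **Other treatments (Introduction).** The conservative options are described as "such as acupuncture, massage, herbal compresses, low frequency therapy, and microwaves, all of which are effective". Massage, which is the control treatment, is among them.
- **Allocation (2.1.5).** "randomization was carried out using a table of random values compiled by SPSS 23.0 software", and patients were "randomly divided into 3 groups with a 1:1:1 allocation ratio", 30 per arm. No stratification factor is named.
- **Blinding (2.1.5).** "In this study, only the assessors were blinded".
- **Analysis (2.2.2).** Groups are compared by MANOVA. No covariate or stratum is named.
- **Records (2.2.4).** Withdrawals, drop-outs, their reasons and compliance are documented, and a case report form is completed. Co-treatment is not mentioned.

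**The concern.** The trial asks whether adding sling exercise to Long manipulation, or giving Long manipulation in place of massage, changes pain, disability and muscle fatigue at 4 weeks. A rehabilitation department may well give its patients other physical treatment alongside the trial; that is an inference, since the article does not describe usual care there.

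Patients and therapists know the allocation. If one arm is seen as weaker, its patients may seek, or be given, more additional treatment, and the 4-week difference then mixes the assigned treatment with the additions. Blinding the assessor does not remove this, because the extra treatment acts on the outcome itself and not on how it is rated. If use is not recorded, it can be neither detected nor explored afterwards.

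The mix of inpatients and outpatients raises a separate and smaller question: whether an unlucky split of the two settings over arms of 30 makes the result less precise or harder to interpret.

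**Working it through.** The plan gives no figure for co-treatment or for the share of inpatients. From the plan come 90 patients in three arms of 30 (2.1.5, 2.2.1) and α = 0.05. The sample size is not in dispute: with f = 0.30, three groups, two measurements and an assumed correlation of 0 between them, the repeated-measures F test needs 79 for power 0.92. That is 81 as a multiple of 3 (power 0.928), and 81 × 1.11 = 89.9, so 90. Every other input below is an assumption.

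**1. Co-treatment that differs by arm after randomisation**

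Bias in a pairwise contrast = (difference in proportion using co-treatment) × (effect of co-treatment in SD units). The standard error of a 30 v 30 contrast is √(2/30) = 0.258 SD. The false-positive rate is 1 − Φ(1.96 − bias/SE) + Φ(−1.96 − bias/SE).

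| Difference in use | Effect | Bias | Bias/SE | False-positive rate (nominal 5%) |
|---|---|---|---|---|
| 20 points | 0.5 SD | 0.10 SD | 0.39 | 6.7% |
| 30 points | 0.8 SD | 0.24 SD | 0.93 | 15% |
| 50 points | 0.8 SD | 0.40 SD | 1.55 | 34% |

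**2. Co-treatment or setting unrelated to arm**

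In 20,000 simulated trials with three arms of 30, 50% use, a 0.8 SD effect, no stratification and no true arm difference, the three-arm F test rejected in 5.0%. Type I error is unaffected.

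**3. Precision lost by ignoring setting**

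If a proportion p are inpatients and the settings differ by g within-setting SD, setting adds p(1 − p)g² to a within-setting variance of 1.

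- p = 0.3, g = 0.3: 0.21 × 0.09 = 0.0189, and 0.0189/1.0189 = 2% of the total variance.
- p = 0.5, g = 0.8: 0.25 × 0.64 = 0.16, and 0.16/1.16 = 14%.

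**4. Chance of an unlucky split without stratification**

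Exact probabilities when the inpatients fall at random over three arms of 30:

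| Inpatients among 90 | Gap ≥ 6 between two named arms | Gap ≥ 6 between largest and smallest arm |
|---|---|---|
| 27 (30%) | 12% | 26% |
| 45 (50%) | 16% | 33% |

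A gap of 6 is 20 percentage points. If the 4-week VAS change differed by 1 point between settings, such a gap would move the contrast by 0.20 × 1 = 0.2 points.

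**The case against.** **The article is condensed.** Concomitant-treatment rules and case report form fields often sit in the full protocol or the operating procedures, which are not shown, and the article neither contradicts itself here nor says that co-treatment is allowed. This limits the point: it cannot be said that the trial has no such rule. But the eligibility criteria are printed as numbered lists, the three regimens are specified in detail, and the items to be recorded are named. On what is printed, a patient receiving any of the treatments named in the Introduction can enter any arm.

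**One unstratified list.** A reader might infer that all 90 patients are drawn from a single list. Section 2.1.5 names no stratum, but it does not rule one out either, so this is an inference from silence.

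**Confounding by setting or earlier treatment.** A reader might also conclude that mixing inpatients and outpatients, or carry-over from earlier treatment, confounds the comparison. It does not. Both are fixed before allocation, randomisation balances them in expectation, and chance imbalance is already covered by α, as step 2 shows. The 33% in step 4 looks alarming, but it is the largest gap among three arms; for a named contrast the chance is 16%. The resulting 0.2-point VAS shift is small and rests on two assumed inputs.

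**No evidence of unequal use.** Nothing in the article shows that co-treatment will differ by arm. That stands, and step 1 therefore shows what could happen and is not a forecast.

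**Conclusion.** The point holds for co-treatment after randomisation. The printed criteria admit patients whatever other neck treatment they receive, the protocol regards such treatment as effective, the arms are open to patients and therapists, and nothing printed would equalise or reveal differential use. The possible bias runs from 0.10 SD to 0.40 SD over the assumed range in step 1. It is near zero if use is similar in all arms, and the documents do not say which case applies.

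For setting and prior treatment the conclusion is weaker: the test remains valid. The cost is about 2–14% of outcome variance left unexplained, if settings differ by 0.3–0.8 SD, and a 12–16% chance of a gap of 6 or more inpatients between two named arms, if 30–50% are inpatients. Stratifying is an inexpensive improvement and does not repair a bias.

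This should be put right before enrolment, because treatment use that was not recorded is hard to reconstruct later.

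**What to change.** 1. **Section 2.1.5:** stratify the randomisation by inpatient or outpatient setting. **Section 2.2.2:** include setting in the between-group model.
2. **Section 2.2.4 and the case report form:** record recent and concurrent neck treatment for every patient, report it by arm, and run a sensitivity analysis if use differs.
3. **Protocol text:** have the investigators state one concomitant-treatment rule that applies equally to all three arms. What it permits or restricts is a clinical decision and is left to them.

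Items 2 and 3 address the possible bias; item 1 addresses precision and the unlucky split. The cost is two allocation lists and one added case report form field, with no change to the sample size. If the full protocol already contains these provisions, stating them in the article is enough.

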#### Ethics approval and consent to participate

2.1.3

The study will be conducted in strict accordance with the principles of the Declaration of Helsinki on Clinical Research.^[7]^ The trial protocol has been endorsed by the Research Ethics Committee of Ningbo College of Health Science (2021-12-07). All participants will be given sufficient time to sign an informed consent form prior to studying.^[8,9]^ This study protocol has been registered with the Chinese Clinical Trials Registry (ClinicalTrials.gov, ID: ChiCTR2100054978).

#### Intervention

2.1.4

The control group will receive conventional message treatment: the treatment plan is based on “Tui-na”, edited by Juntao Yan^[10]^: the patient is seated and relaxes the muscles of the neck, shoulders, and upper back; the patient then takes and rubs the cervical tension and spasm, presses and rubs the painful points of the neck nodes with the finger, continues 3 to 5 times, then presses the acupoints of Tianzhu, Fengchi, Fengfu, cervical spine and Dazhi with the thumb, each point for 1 minute; gently presses the neck and shoulder muscles with palm rubbing, and then applies the cervical oblique pulling method and stretches at the end position for 5 seconds. The treatment is repeated 3 to 5 times. The treatment was repeated 3 to 5 times; 30 min/time, 1 time/d, 5 times/wk, 4 weeks in total.

The Long manipulation group will be treated with Long manipulation^[11]^: a 4-step intervention using the Long manipulation method of orthopedics massage: relaxation technique, orthopedics technique, strengthening technique and pain zone technique. After relaxing the cervical tissues with kneading in the recumbent position, the cervical spine will be orthopedic stabilized corresponding to the type of misalignment: cervical axis alteration and anterior-posterior slippage misalignment with lateral pushing, left-right rotation misalignment with low head shaking, lateral bending and side-swinging misalignment with lateral moving, spine gap stenosis or mixed misalignment with traction chair orthopedics correction, followed by tendon division and tendon management in the soft tissues of the neck to regain the dynamic and static balance of the cervical spine. Finally, the hurting areas of the shoulders, back and upper limbs are treated with kneading and kneading techniques. The above treatments are given for 20 minutes each time, once a day for 4 weeks.

The combined treatment group combines SET on the basis of the Long manipulation group, in which the procedure for Long manipulation is the same as above and the treatment for SET is shown as follow^[12]^: before the start of the treatment look for weak chains, determine the stability and muscle tension of the neck muscle groups and assess the muscle strength of the flexor muscle groups on both sides of the collar to develop a training protocol. Active exercise: the patient is placed in a supine position with slightly flexed knees, the thoracic spine and pelvis are immobilized with elastic cords and the head is secured with a central parting band. The patient is asked to flex the left side, flex the right side, flex the front, expand the back and rotate the neck to the maximum degree and hold for 5 seconds; each dimension is done 5 times and counted as 1 set, a total of 5 sets are completed with 30 seconds rest between sets. Slow, controlled, stable, and pain-free movements of 30 minutes, 5 times/wk for 4 weeks; The study protocol was designed in accordance with the recommendations of the standard program project: intervention trials recommendations 2013 statement. (Table 1; Additional File 2)

**Table 1 T1:** Standard protocol items: recommendations for intervention trials (SPIRIT) figure of the Long manipulation study protocol.

	Time	
Contents	0 wk	4 wk
Screening participants	×	
Sign informed consent	×	
Randomized	×	
Interventions		
Combine treatment group	×	×
Long manipulation group	×	×
Control group	×	×
Evaluation of therapeutic effect:		
VAS score	×	×
NDI score	×	×
SMEG assessment:		
MPF and PF of the bilateral superior	×	×
Oblique and sternocleidomastoid muscles	×	×

MPF = mean power frequency, NDI = Neck Disability Index, SMEG = surface electromyography, VAS = visual analogue score.

#### Randomization, allocation, and blinding

2.1.5

In this study, randomization was carried out using a table of random values compiled by SPSS 23.0 software, and the patients were randomly divided into 3 groups with a 1:1:1 allocation ratio: the combined treatment group (30 cases), the Long manipulation group (30 cases) and the control group (30 cases). Only the principal investigator in this study will be aware of the order of random assignment. The assessor will be a trained external rehabilitation therapist. The assessor and the patient will not be able to communicate about the intervention during the assessment. In this study, only the assessors were blinded and therefore the study did not involve the process of unblinding.

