#### Assess safety

2.1.7

To maintain the safety of the subjects participating in this study, the project leader will supervise the data collection process. During each monitoring session subjects will be asked to remain in hospital for 30 minutes after treatment and will be asked if there are any possible signs of discomfort during the trial. Side effects following the intervention will be recorded during each treatment session.

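### The principal investigator holds the whole random order, and nothing in the article separates that role from recruitment or eligibility decisions, so allocation concealment is not assured

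*Protocol article*

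**What the plan says.** Section 2.1.5 (Randomization, allocation, and blinding) states that "randomization was carried out using a table of random values compiled by SPSS 23.0 software" and that "the patients were randomly divided into 3 groups with a 1:1:1 allocation ratio", with 30 patients per group. On access to the list it says "Only the principal investigator in this study will be aware of the order of random assignment". It adds that the assessors alone are blinded, and that the assessor is an external therapist who may not discuss the intervention with the patient.

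Other sections describe who does what:

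- Section 2 (Method/design): "The project leader will be responsible for the overall project and will initiate the establishment of the subject project team". The next sentence reads "The subject project team will be responsible for subject security, recruitment and treatment and assessment, and quality control".
- Section 2.1.2 (Exclusion criteria): "Potential subjects who meet the requirements will be interviewed by the research staff". One of the exclusions is "Those who do not collaborate with study".
- Section 2.1.7 (Assess safety): "the project leader will supervise the data collection process".

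On timing, Section 2 puts the week-0 assessment after randomization, whereas Section 2.1.2 describes a baseline assessment as part of the work-up for eligibility.

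**The concern.** Concealment means that nobody who can influence whether, or when, a patient enters the trial knows which arm comes next. The usual protection is to keep the list with someone outside enrolment. This plan names an investigator as holder and says nothing that keeps that investigator away from entry decisions.

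Foreknowledge could act here because entry involves judgement. Eligibility rests on clinical presentation, examination and imaging, and one exclusion turns on whether a patient is thought willing to cooperate. A patient expected to do well could be entered when a favoured arm is next, and deferred or judged uncooperative when it is not.

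The trial has few other protections. Only assessors are blinded. The VAS is the patient's own score, and the Neck Disability Index asks about the patient's pain and daily activities, so it is taken here to be self-rated as well. Adjustment for week-0 VAS and NDI could remove part of an imbalance created at entry, but not the part due to unmeasured prognosis.

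**Working it through.** No arithmetic applies, because the plan gives no figure on this point. The check is to set the sections side by side.

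1. **Who knows the order?** The principal investigator, and nobody else (Section 2.1.5). The order of assignment covers future patients as well as those already entered, so this is advance knowledge.

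2. **Who recruits and meets candidates?** The project team (Section 2) and the research staff (Section 2.1.2). Neither section says whether the principal investigator belongs to these groups.

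3. **Who decides eligibility?** Section 2.1.2 describes the diagnostic steps but does not say who takes the decision. The principal investigator is neither named nor ruled out.

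4. **Is the principal investigator the project leader?** Section 2.1.5 uses the first title; Sections 2 and 2.1.7 use the second. In a single-centre trial they may well be one person, but no sentence says so.
   - If they are the same, the list holder also sets up the team that recruits, treats and assesses, and supervises data collection.
   - If they differ, the list holder is still an investigator whom no section keeps apart from entry decisions.

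5. **Does other oversight close the gap?** Section 2.2.4 sends two supervisors each month to check that enrolled patients meet the criteria. Section 2.2.3 has two independent researchers record data and makes the college responsible for supervision and quality control. These checks look at patients who were entered. They cannot show that an eligible patient was deferred or turned away, which is how selection would operate.

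6. **When is the patient committed?** Sections 2 and 2.1.2 leave it unclear whether baseline is measured before or after the arm is fixed. Releasing the assignment only after the week-0 assessment would settle this, but it contradicts the order now in Section 2.

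Steps 1 to 4 give the result: under either reading of the two titles, the person who knows the upcoming assignments is not shown to be independent of enrolment. Steps 5 and 6 show that nothing else in the article supplies that independence.

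**The case against.** The strongest reply is that Section 2.1.5 can be read as a safeguard. If the principal investigator alone knows the order, the staff who recruit and interview do not. Concealment fails only if the principal investigator enrols patients, rules on eligibility or passes on the order, and the article reports none of these. This stands, and it limits the point to concealment that is not assured.

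Three stronger readings are tempting, and the article does not support them:

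- A reader might infer that allocation is open to those who enrol patients. On its face, the sentence on access says the opposite for everyone but the principal investigator.
- A reader might infer that the project leadership runs recruitment. Section 2 gives recruitment to the team; the leader sets that team up. Carrying this over to the principal investigator also requires treating the two titles as one person.
- A reader might infer that supervising data collection with the list in hand breaks the assessor blind. The assessor is external, no section has the leader attend or score assessments, and knowledge of the future order adds little once treatment is visible to staff. That would in any case be a question of detection bias after assignment, separate from concealment at entry.

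It can also be said that a journal article may leave the release mechanism, such as envelopes or a central service, to the full protocol. That is right, and the missing mechanism is not part of this point. The choice of list holder is different, because the article states it.

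**Conclusion.** The concern holds in a limited form. The plan gives the full sequence to an investigator whose separation from recruitment and eligibility decisions is not established. Allocation concealment is therefore not assured in a trial with blinded assessors only and outcomes that rest largely on the patient's own rating.

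The size of any bias cannot be derived. The article gives no basis for how far selection might shift the prognosis of one arm, and any figure would only restate an arbitrary assumption.

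The conclusion does not depend on the principal investigator and the project leader being the same person; if they are, the weakness is greater. It does rest on no fuller document, not shown here, already keeping the principal investigator out of entry decisions. It should be fixed; confidence is medium.

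**What to change.** In Section 2.1.5, replace the sentence on access with wording such as: *The allocation sequence is held by a named staff member who takes no part in recruiting, treating or assessing patients. The principal investigator and anyone who judges eligibility do not see upcoming assignments. Each assignment is released singly, after consent and eligibility have been recorded and the week-0 assessment has been done.*

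Amend Section 2 so that the week-0 assessment comes before randomization; otherwise the two sections will conflict.

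Coordinating-centre staff are one possible holder. Section 2 gives them only communication and information duties, so their independence from recruiting, treating and assessing must be confirmed first. If the principal investigator has already seen the list, handing it over does not restore concealment, and the new holder should regenerate the unused part.

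The cost is two changes of wording and a small administrative task for existing staff. Sample size, visits and treatments are unaffected.
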